The existence of a widely reported cross-education effect, particularly for variables related to muscle function, can be considered a limitation of this design. However, there is a growing trend in strength training research suggesting that, despite this effect, experimental designs comparing active unilateral strength training interventions (ie, with the control limb remaining nonsedentary) performed on each limb of the same individual are more suitable than designs comparing interventions in 2 different groups of people, even if randomized [53]. This is justified by the greater control in such experimental designs over intrinsic factors (eg, gene expression of protein transcription factors, muscle fiber type distribution, and capillary-to-fiber ratio) and extrinsic factors (eg, sleep quality, training level, and diet), which are known to influence responses to strength training and cannot be controlled in designs involving different individuals in groups. Furthermore, when the primary outcome of the investigation is muscle hypertrophy, the unilateral training design appears even more suitable, as there is evidence that there is no cross-education effect for this type of outcome [54-56].

Neuromuscular function and body composition markers will be collected 1 week before and 1 week after the interventions and compared between limbs. The VL performed in each training session and the session’s perceived effort will be recorded for comparison over time and between limbs. The experimental design of the study is illustrated in Figure 1.

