### Markers of Neuromuscular Adaptation to Training Protocols

Body composition of both arms will be determined using dual-energy x-ray absorptiometry (DXA; Lunar, iDXA, GE Healthcare) in a supine position. The variable of interest for this study will be the muscle mass of the arm and the entire upper limb of the participants.

The thickness of the biceps brachii and brachialis muscles will be determined at 3 locations, based on percentages of the distance between the posterior margin of the acromion of the scapula and the olecranon of the ulna, namely proximal (50%), middle (60%), and distal (70%) [58], using images obtained by a mode-B ultrasound device (Saevo FP 102, Ribeirão Preto) with a 40 mm linear transducer and a frequency of 10 MHz. Participants will remain in a supine position for 5 minutes before recordings to allow for fluid accommodation. The transducer will be positioned perpendicularly to the skin over the muscle and transversely to the limb. Three images of each assessed region of both muscles will be captured and exported. The ImageJ software (National Institutes of Health) will be used to determine the thickness of each muscle by calculating the difference between the superficial and deep fascias, as well as the total muscle compartment thickness, by calculating the difference between the superficial fascia of the muscle compartment and the osteomuscular interface. Reliability of ultrasound measurements will be carried out by means of the intraclass correlation coefficient.

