Muscle function will be evaluated using an isokinetic dynamometer (System 4, Biodex Systems) with participants positioned on a preacher curl bench set at a 45º angle adjusted to the dynamometer. Peak isometric torque and maximum rate of torque development (RTD) will be determined from 2 maximal voluntary isometric contractions of 5 seconds at 2 different angles, 60º and 90º of elbow flexion, with a 1-minute interval between each attempt. After proper positioning on the dynamometer, following the manufacturer’s instructions, and a standardized warm-up (5 minutes of exercise with a self-selected load on a stationary bike followed by 3 submaximal isometric contractions), participants will be instructed to flex the assessed elbow as quickly and with as much force as possible, sustaining the maximal contraction for 5 seconds. A 1-minute rest will be observed between the 2 contractions at each angle. The torque-time curves will be filtered and analyzed in MatLab (Mathworks, IBM), with the highest torque value recorded in the 2 contractions considered as peak isometric torque and the steepest slope of the torque-time curve as RTD. These procedures will be performed for each investigated angle (ie, 60º and 90º of elbow flexion). The contraction with the highest torque value will be used for analysis. Peak torque will be calculated as the highest value on the torque-time curve. The maximum RTD will be calculated as the steepest slope of the torque-time curve. The onset of muscle contraction will be defined as the point where torque values exceed 2.5% of the difference between baseline and peak torque values [59]. For more details on the procedures for filtering and analyzing isometric torque data, refer to [60]. Three minutes after the assessment of isometric strength, dynamic muscle function will be evaluated using nonintercalated maximal isokinetic concentric and eccentric contractions. First, 5 maximal isokinetic concentric contractions of the elbow flexors will be performed with a range of motion of 100° (10º-110º of elbow flexion) at an angular velocity of 60°/s. This range of motion was chosen to allow for greater joint comfort during movement, avoiding full extension at 0º at the beginning of the movement. Additionally, a semipronated grip at 30º is standardized for greater wrist joint comfort. The interval between contractions will be approximately 1.5 seconds, while the dynamometer arm returns passively to the initial position. After a 3-minute recovery interval, 5 maximal isokinetic eccentric contractions of the elbow flexors will be performed with the same range of motion (100°: 10º-110º), angular velocity (–60°/s), and interval between contractions. The highest torque values produced for each contraction will be recorded, and the average of the highest values from the 5 contractions (for each type of contraction) will be calculated and recorded as concentric torque peak and eccentric torque peak.

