### Statistical Treatment

A formal a priori power analysis was conducted using G*Power software (version 3.1.9.7; Heinrich-Heine-University Düsseldorf). The calculation was based on an effect size of 0.57 [61], for a study that observed significant increases in elbow flexor muscle thickness following resistance training performed to failure, also over a 10-week period. Considering a power (1-β) of .80, a significance α level of .05, and a 2-tailed test for repeated measures (within-subject design), the estimated required sample size was 21 upper limbs. Accordingly, the minimum number of participants needed was 11, assuming each would complete both unilateral protocols. This estimation was based on a 10-week intervention period and informed the recruitment target of this study. The normality of data distribution will be assessed using the Shapiro-Wilk test. Nonparametric data will undergo a logarithmic transformation. The assumptions of homogeneity and sphericity of the data will be checked using Levene and Mauchly tests, respectively. Comparisons over time and between limbs for all dependent variables will be conducted using a 2-way mixed model ANOVA for repeated measures (time effect) and nonrepeated measures (limb effect). If significant effects of limb or time are identified, Bonferroni post hoc adjustments will be applied. Main effect sizes will be calculated and expressed as partial η². If significant interaction effects between limb and time are detected, pairwise comparisons between relevant points will be performed. Effect sizes for significant differences in dependent variables between limbs or over time will be calculated and expressed as Cohen *d*. The significance level adopted will be *P*<.05.

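### No single deciding outcome is fixed: 17 pre/post outcomes are each tested at P<.05 with no control across outcomes, which raises the chance of a false limb difference well above 5% in most plausible settings

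*Protocol article*

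**What the plan says.** Under Statistical Treatment, "Comparisons over time and between limbs for all dependent variables will be conducted" with a two-way mixed ANOVA, time being repeated and limb nonrepeated. One threshold, P<.05, covers everything. The only multiplicity step is this: "If significant effects of limb or time are identified, Bonferroni post hoc adjustments will be applied". That step operates inside one outcome's ANOVA.

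Under Experimental Design, the only mention of a primary outcome is a general argument for unilateral designs: "when the primary outcome of the investigation is muscle hypertrophy, the unilateral training design appears even more suitable". The sample size rests on an effect of 0.57 for elbow flexor thickness, with no muscle or site named.

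The outcomes are set out under Markers of Neuromuscular Adaptation to Training Protocols:
- Ultrasound gives the thickness of two muscles at the 50%, 60% and 70% sites, "as well as the total muscle compartment thickness".
- DXA gives muscle mass of the arm and of the whole upper limb.
- Isometric peak torque and rate of torque development are taken at 60º and 90º: "These procedures will be performed for each investigated angle".
- Isokinetic testing gives one concentric and one eccentric peak.

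**The concern.** Hypotheses 2 and 3 concern morphology and muscle function as groups. The article does not say which result would settle either one. Every member of each group is tested at the same nominal level with the same standing, so the more sites, angles and contraction types there are, the likelier it is that at least one differs between limbs by chance.

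Timing adds to this. The Results section reports 7 participants finished, against a stated minimum of 11. Table 1 schedules data analysis in October-December 2024, before the collection planned for 2025. The longer the deciding outcome stays open, the harder it becomes to show that it was chosen independently of the data.

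**Working it through.** The article states no error rate across outcomes, so there is no figure of its own to reproduce here.

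**Step 1. Count the pre/post outcomes** (Markers of Neuromuscular Adaptation to Training Protocols).
- Ultrasound: 3 sites × 3 thicknesses (biceps brachii, brachialis, total compartment) = 9.
- DXA: 2.
- Isometric: 2 measures × 2 angles = 4.
- Isokinetic: 2.
- Total: 9 + 2 + 4 + 2 = 17. Volume load and perceived exertion are extra.

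**Step 2. Inputs.** Alpha is .05 per outcome and tests are two-sided (Statistical Treatment), so each test allows .025 in the ECC+ direction. There are 11 participants. One limb-by-time test is counted per outcome. The correlation between outcomes is not given and is therefore assumed.

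**Step 3. Independent outcomes, paired test.**
- Any false limb difference: 1 − 0.95^17 = 58.2%.
- At least one false ECC+ advantage: 1 − 0.975^17 = 35.0%.
- The 11 morphology measures alone (9 + 2): 1 − 0.95^11 = 43.1% in either direction; 1 − 0.975^11 = 24.3% for ECC+.

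**Step 4. Correlated outcomes, paired test.** Simulation of 40,000 runs with 17 equally correlated limb differences, n = 11, t on 10 df, two-sided .05:

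| Assumed correlation between outcomes | Either direction | ECC+ direction |
|---|---|---|
| 0 | 58% | 35% |
| 0.3 | 51% | 26% |
| 0.5 | 41% | 21% |
| 0.7 | 30% | 15% |

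Correlation that is higher within the DXA, ultrasound and strength groups than between them (0.5 to 0.8 within, 0.1 to 0.4 between) gives 33-49% in either direction and 17-26% for ECC+.

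**Step 5. The test as planned.** With two time points and limb nonrepeated, the limb-by-time test is an unpaired comparison of change scores on 2 × 11 − 2 = 20 df. It is conservative when a participant's two arms change alike. For 17 independent outcomes, by simulation:

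| Assumed correlation between the two arms' changes | Either direction |
|---|---|
| 0 | 58% |
| 0.3 | 32% |
| 0.5 | 15% |
| 0.7 | 3% |

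In the ECC+ direction the rates at 0.3 and 0.5 are about 17% and 7%. If outcomes are also correlated at 0.5, they fall to about 11% and 5%.

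**The case against.** **The headline size can be overstated.** A reader might infer that a false ECC+ advantage is more likely than not, or 30-40% likely with correlated outcomes. The documents do not support that. The 58%, 41% and 30% count false differences in either direction, including those favouring TRAD. For ECC+ alone the figures are 35%, 21% and 15%.

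**Independence is unrealistic.** Total compartment thickness overlaps the two muscles it spans, and the DXA arm region lies within the upper limb. This stands, and it makes 58% an upper reference point only.

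**The planned ANOVA is not the paired test.** This also stands. Experimental Design justifies the within-person comparison by factors shared between the arms, which is the condition under which the planned test is conservative. At an arm correlation of 0.7 the rate over 17 independent outcomes is about 3%. But that protection comes from ignoring the pairing. It disappears once the analysis matches the design, and it is not multiplicity control.

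**Hypertrophy is already the main domain.** The design argument, the sample-size basis and the Conclusion all point that way. That narrows the field to 11 measures but does not choose among them.

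**The detail may be left to a fuller document.** The article does not leave the matter open, however. It states the scope, the threshold and where Bonferroni applies, and that stated rule is what is at issue.

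**Selective claiming is not shown.** A reader might infer that one site would be enough to call a hypothesis confirmed. No passage says so. The Conclusion's remark on specific areas of the muscle is conditional and follows a regional rationale given in advance.

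**Conclusion.** The concern holds in this form: 17 pre/post outcomes share one uncorrected threshold, and no single measure is fixed as deciding.

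Under a paired test, at assumed between-outcome correlations from 0 to 0.7, the chance of a false limb difference in either direction is 58% down to 30%, against 5% for one test. The chance of a false ECC+ advantage is 35% down to 15%, about 14 to 6 times the nominal 2.5% (35/2.5 = 14; 15/2.5 = 6). Under the planned unpaired limb comparison the rate is lower, and it can fall below 5% if the two arms change very much alike. The actual rate therefore depends on two correlations that the article does not give. All figures count one limb-by-time test per outcome and assume no true difference on any outcome.

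The plan should be changed, but this does not invalidate the trial.

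**What to change.** In Statistical Treatment:
1. Name one primary outcome from data already collected and consistent with the thickness basis of the sample size. One example is total elbow-flexor compartment thickness averaged over the 50%, 60% and 70% sites. Test it once, by the paired between-limb difference in change at two-sided .05. That brings the primary error rate to 5% (2.5% in the ECC+ direction). Do not describe it as the same measure that gave the 0.57: the article does not say which muscle or site that came from.
2. Make all other outcomes secondary, including the site-specific thicknesses that carry the regional question. Either apply Holm within the morphology family and within the strength family, or report estimates with 95% CI and no confirmatory claim.
3. State that the choice was made after 7 participants had completed, and whether any between-limb results had been seen by then.

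The cost is more than wording. Some secondary outcomes lose nominal significance: with the 11 individual morphology measures in one family, Holm's first step is .05/11 = .0045, and with 6 strength measures it is .05/6 = .0083. The regional question is no longer part of the primary test. A choice made this late needs the disclosure in item 3 to be credible. No new measurement is needed.

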### Experimental Design

The study will be conducted as a within-participant randomized trial. Each participant will undergo 2 different interventions over 10 weeks, each being performed on one of their upper limbs, with 2 training sessions per week separated by a minimum of 48 hours and a maximum of 96 hours. The intervention for each participant’s upper limb will be randomly assigned via electronic randomization. Using commonly available online randomization tools, the first randomization draw will determine whether the left or right upper limb will be selected. Next, the intervention to be applied to the previously selected limb (traditional or ECC+) will be randomly selected. Finally, a randomization draw will decide whether the previously selected protocol and limb will be conducted before or after the unselected protocol (ie, both protocols will be performed in the same session). No counterbalancing based on limb dominance (ie, right-handedness) will be implemented in either the applied protocol or the order of performance. The limb assigned to traditional training (TRAD) will follow a protocol with sets of repetitions until concentric failure (MF_CON_). The limb assigned to the eccentric overload training protocol (ECC+) will follow the same exercise protocol, but with the addition of exclusively eccentric contractions until eccentric failure (MF_EXC_) after reaching MF_CON_.

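### The planned ANOVA treats limb as an independent-groups factor although every woman contributes both arms, so the pairing that justifies the design is lost from the analysis

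*Protocol article*

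**What the plan says.** The Experimental Design section is explicit about the unit: "The study will be conducted as a within-participant randomized trial", and "Each participant will undergo 2 different interventions over 10 weeks, each being performed on one of their upper limbs". It prefers this to a comparison of separate groups of people because the two arms share biology and circumstances: "This is justified by the greater control in such experimental designs over intrinsic factors", followed by extrinsic factors such as sleep and diet.

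The Statistical Treatment section then fixes one analysis for every outcome, namely a "2-way mixed model ANOVA for repeated measures (time effect) and nonrepeated measures (limb effect". So time is the repeated factor and limb the nonrepeated one, for all outcomes. The same section adds: "The assumptions of homogeneity and sphericity of the data will be checked using Levene and Mauchly tests, respectively". It does not say which groups the Levene test compares. The abstract mentions only a two-way ANOVA. Nowhere is a participant effect added or limb declared a repeated factor.

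**The concern.** A nonrepeated factor has different, independent units at each of its levels. Here the same women supply both levels. Calling the model mixed does not rescue it, because the sentence itself defines the mix as time repeated and limb nonrepeated.

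Two tests are affected, in different ways. Limb-by-time carries the hypotheses that morphology and function improve more with ECC+. Stable differences in level between women already drop out of that test, because time is repeated. What stays wrongly in its error term is the variation between women in how much they change, which a paired comparison would remove. The time effect is averaged over both arms and is tested as if the arms were separate people.

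At stake are a test of ECC+ against TRAD that may miss a real benefit in a trial with a minimum of 11 women, and a time effect that may look firmer than it is.

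**Working it through.** **Inputs**
- Women, n = 11: the minimum stated in Statistical Treatment. Each has two arms, giving 22 limbs.
- Assessments: one before and one after the intervention (Experimental Design).
- Difference used for power: 0.57 SD of change. The article says "The calculation was based on an effect size of 0.57" without stating which kind of effect size this is, so reading it in SD of change is my assumption.
- Two-sided alpha of 0.05.
- Correlation rho between the changes in a woman's two arms: not given, so shown as a range.

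**The plan's own figure.** The article gives 21 upper limbs, taken as 11 participants. A two-tailed paired t test with a standardised paired difference of 0.57 and 80% power needs 27 pairs; a one-sided test needs 21. The figure is therefore not reproduced on that reading. That is a separate matter, and only n = 11 is carried forward.

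**Formulas.** Let s be the SD of change in one limb.
- ECC+ change minus TRAD change: true variance 2s²(1-rho)/n. The planned model uses 2s²/n, a ratio of 1/(1-rho).
- Mean change over both arms (time): true variance s²(1+rho)/(2n). The planned model uses s²/(2n), a ratio of 1/(1+rho).
- Error degrees of freedom: planned 2n-2 = 20; within-participant n-1 = 10.

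**Numbers at rho = 0.5, s = 1**
- Limb-by-time: true variance 2 × 0.5/11 = 0.091 (SE 0.30); planned 2/11 = 0.182 (SE 0.43). A difference of 0.57 is 0.57/0.302 = 1.89 true standard errors, but 0.57/0.426 = 1.34 as the planned model measures it.
- Time: true variance 1.5/22 = 0.068 (SE 0.26); planned 1/22 = 0.045 (SE 0.21).

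**Simulation** (200,000 trials per row, n = 11)

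| rho | 1/(1-rho) | 1/(1+rho) | Type I error, limb-by-time, planned | Type I error, time, planned | Power at 0.57 SD, planned | Power at 0.57 SD, paired |
|---|---|---|---|---|---|---|
| -0.3 | 0.77 | 1.43 | 8.5% | 2.1% | 28% | 19% |
| 0 | 1.00 | 1.00 | 5.1% | 4.9% | 25% | 23% |
| 0.3 | 1.43 | 0.77 | 2.3% | 8.2% | 21% | 30% |
| 0.5 | 2.00 | 0.67 | 0.9% | 10.7% | 18% | 40% |
| 0.7 | 3.33 | 0.59 | 0.2% | 13.1% | 15% | 60% |

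The within-participant analysis keeps type I error at about 5% for both tests in every row.

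**The case against.** The best reply is that the size, and even the direction, of the harm depends on a correlation the article never gives. That stands. At rho = 0 the error variances agree, only the degrees of freedom are wrong, and the planned test has slightly more power (25% against 23%). At negative rho the directions reverse. The article's own case for the design, that the arms share what drives the response, implies a positive rho but does not quantify it. It can also fairly be said that, at positive rho, the test of ECC+ against TRAD is conservative, so it would not falsely favour ECC+, and that the time effect is not itself a stated hypothesis.

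Three stronger readings are tempting, but the documents do not support them:
- A reader might infer that the model contradicts the sample size calculation, which assumes "Considering a power (1-β) of .80, a significance α level of .05, and a 2-tailed test for repeated measures (within-subject design". But within-subject there may mean before and after within one limb: the effect size comes from a study of thickness gains over 10 weeks, and the result is counted in limbs. The clear conflict is with the design.
- A reader might infer that the volume-load comparison would lose almost all its power. No between-limb correlation is given for it. The Monitoring of VL section counts the extra eccentric repetitions at half weight on top of otherwise matching sets, so a higher value in ECC+ is expected by construction. Volume load is also recorded at every session, so stable level differences do not enter its limb-by-time test.
- A reader might infer that the trial's confidence intervals will be too wide. The section plans none; it names P values, partial η² and Cohen d.

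**Conclusion.** The point holds. The named model does not fit the design whatever rho is, and because each factor is explicitly classified, this is a misstatement and not a detail left for later. Given a positive rho, the comparison of protocols loses power and the time effect is overstated. At rho = 0.5 with 11 women, power for 0.57 SD of change is 18% where pairing gives 40%, and the time test has 10.7% type I error. These sizes rest on an assumed rho, exactly 11 completers and 0.57 read in SD of change; they illustrate the loss and do not forecast this trial's power. The mismatch should be corrected before the final analysis.

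**What to change.** Replace the ANOVA sentence with a two-way repeated-measures ANOVA in which both limb and time are within-participant factors. For pre/post outcomes, the test of the protocols is then the paired comparison of ECC+ change minus TRAD change on n-1 degrees of freedom (10 with 11 completers).

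A linear mixed model with random effects for participant and limb within participant is an alternative, provided it also has a participant-by-time term. The first two alone leave the changes in a woman's two arms uncorrelated, so they bring back the same limb-by-time and time error terms as the planned ANOVA.

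A Levene test that treats the limbs as independent groups is then not needed.

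The cost is one sentence. Data, participants and conduct are unchanged. The Results section reports 7 completers with further collection planned, so the change can precede the final analysis.
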